# Efficacy and safety of Shi-style cervical manipulation therapy for treating acute and subacute neck pain: study protocol for a randomized controlled trial

**DOI:** 10.1186/s13063-021-05062-6

**Published:** 2021-02-08

**Keywords:** Acute neck pain, Subacute neck pain, Shi’s cervical manipulation, Effectiveness, Safety, Diclofenac sodium sustained-release capsules

## Abstract

**Background:**

Neck pain is a common clinical disease, which seriously affects people’s mental health and quality of life and results in loss of social productivity. Improving neck pain’s curative effect and reducing its recurrence rate are major medical problems. Shi’s manipulation therapy has unique advantages and technical features that aid in the diagnosis and treatment of neck pain. Compared with first-line non-steroidal anti-inflammatory drug (NSAID) treatment of neck pain, Shi’s cervical manipulation lacks the relevant research basis of therapeutic advantage, safety, and satisfaction for treating acute and subacute neck pain. Herein, we aim to confirm our hypothesis in a clinical trial that the safety and efficacy of Shi’s cervical manipulation will be more effective, safer, and more satisfactory than NSAIDs to treat acute and subacute neck pain.

**Methods:**

In this multicenter, positive-controlled, randomized clinical trial, traditional analgesic drug (NSAID) is used to evaluate and show that Shi’s manipulation is more effective, safe, and satisfactory for treating acute and subacute neck pain. Overall, 240 subjects are randomly divided into the trial and control groups, with both groups treated by the corresponding main intervention method for up to 12 weeks. Clinical data will be collected before the intervention and immediately after the first treatment; at 3 days and 1, 2, 4, 8, and 12 weeks after the intervention; and at 26 and 52 weeks after treatment follow-up of clinical observation index data collection. The clinical observation indices are as follows: (1) cervical pain is the primary observation index, measured by Numerical Rating Scale. The secondary indices include the following: (2) cervical dysfunction index, measured by patient self-evaluation using cervical Neck Disability Index; (3) cervical activity measurement, measured by the cervical vertebra mobility measurement program of Android mobile phone system; (4) overall improvement, measured by patient self-evaluation with SF-36; and (5) satisfactory treatment, determined by patient self-evaluation.

**Discussion:**

We will discuss whether Shi’s cervical manipulation has greater advantages in efficacy, safety, and satisfaction of acute and subacute neck pain than traditional NSAIDs, to provide a scientific basis for the dissemination and application of Shi’s cervical manipulation.

**Trial registration:**

China Registered Clinical Trial Registration Center ChiCTR1900021371. Registered on 17 February 2019

## Introduction

### Background and rationale {6a}

According to the latest surveys, 71.5% of the general population had neck pain for more than a year [1–3]. Although neck pain caused only 1.7–11.5% of disability, it is worth noting that, equivalent to back pain, it caused a huge burden and disability rate on individuals and the social economy and was listed as 1 of 5 chronic and refractory diseases by the US government. Previous studies confirmed that acute and subacute neck pain is particularly important in the prevention and treatment of neck pain [4, 5]. Patients with acute and subacute neck pain rank significantly lower than healthy people in both mental health and quality of life. In addition, acute and subacute neck pain results in reduced social productivity caused by loss of life function and labor force involvement, and the additional financial burden continues to increase dramatically [6, 7]. How to treat acute and subacute neck pain, improve its curative effect, and reduce recurrence rate are major medical problems faced by people all over the world.

Traditional Chinese medicine (TCM) manipulation therapy has unique advantages and characteristics in the diagnosis and treatment of neck pain. As early as the Qing Dynasty, detailed manual treatment of neck pain was recorded in the Traditional Chinese Medical Orthopedics monograph, *Chinese Bone-setting Diagram*: “If the neck is injured, the head on the back cannot be lowered, or the tendon is long and bone is wrong, or the tendon is gathered, or the tendon is strong, use the second manipulation of *Xiong Gu Zi’s* technique to lift and correct the neck.” On this basis, doctors developed many cervical vertebra techniques and formed different schools with different characteristics and positive curative effects in the diagnosis and treatment of neck pain. “Shi’s Traumatology,” a valuable cultural heritage passed from generation to generation in Shanghai over a hundred of years, is one of the most distinctive schools of “Shanghai culture.” And the cervical vertebra correction technique developed from it, “Dislocation of Bone and Malposition of Ligament,” is mature and effective. Shi’s cervical correction technology can reduce the recurrence rate, improve the efficiency of the price ratio, and support obvious clinical advantages in the diagnosis and treatment of neck pain [8–10]. However, compared with the first-NSAIDs treatment of neck pain, Shi’s cervical manipulation lacks the relevant research basis in terms of efficacy advantage, safety, and satisfaction in the treatment of neck pain.

### Objective {7}

Here, we present the protocol of a multicenter, positive-controlled, randomized clinical study investigating the efficacy and safety of Shi-style cervical manipulation therapy for treating acute and subacute neck pain. Our hypothesis is that Shi’s cervical manipulation would have more advantages in efficacy, safety, and satisfaction to treat acute and subacute neck pain than traditional NSAIDs.

### Trial design {8}

In this study, a multicenter positive-controlled, randomized clinical trial design is used. Patients with acute and subacute neck pain in accordance with the test and research standards are randomly divided evenly into two groups: trial group (with Shi’s manipulation of the cervical spine as the main intervention method) and control group (with oral administration of diclofenac as the main intervention method), with both groups treated by corresponding main intervention method for up to 12 weeks. Clinical data will be collected before the intervention and immediately after the first treatment; at 3 days and 1, 2, 4, 8, and 12 weeks after the intervention; and at 26 and 52 weeks after treatment follow-up of clinical observation index data collection.

## Methods: participants, interventions, and outcomes

### Study setting {9}

This is an exploratory, multicenter, positive-controlled, randomized clinical study. This trial began in October 2019 and ends in October 2021. It is organized and implemented by the Department of Orthopedics and Traumatology of Shuguang Hospital Affiliated with Shanghai University of Traditional Chinese Medicine. The research is planned to be completed in Shuguang Hospital Affiliated with Shanghai University of Traditional Chinese Medicine (Shuguang Hospital for short), Shanghai Jing’an District Central Hospital (Jing’an Center Hospital for short), and Shanghai Xiangshan Hospital of Traditional Chinese Medicine (Xiangshan Hospital for short). Shuguang Hospital is a hundred-year-old hospital in Shanghai. It is a grade III, class A comprehensive hospital of traditional Chinese medicine. It is a national model hospital of traditional Chinese medicine and has three key disciplines of the Ministry of Education. Shi’s orthopedics and traumatology, as one of the key disciplines of the Ministry of Education, has a history of nearly 150 years and is one of the first national intangible cultural hospitals. Jing’an Central Hospital is a grade III, class B general hospital with a history of more than 70 years. It is the teaching hospital of Shanghai Second Medical University, Shanghai University of Traditional Chinese Medicine, and Medical College of Shanghai Tongji University. Xiangshan Hospital is one of the first grade II, class A hospitals of traditional Chinese medicine in Shanghai. It has a history of more than 40 years, which is a hospital of traditional Chinese medicine and integrated traditional Chinese and Western medicine. All three hospitals are responsible for the program’s therapeutic interventions and are located in Shanghai, China, and Shuguang Hospital is the main responsible center of this project. The reasons for choosing these three hospitals as the research centers of this project are as follows, On the one hand, these three hospitals are all located in the center of Shanghai, with dense population and convenient transportation, which is conducive to the treatment and follow-up of the subjects; on the other hand, the orthopedics and traumatology department of these three hospitals is very famous in Shanghai, and Shi’s orthopedics and traumatology department of Shuguang Hospital and the other two hospitals often carry out cooperation in clinical diagnosis and treatment techniques and scientific research. These convenient conditions contribute to the smooth development of this research project. According to the standard implementation method of randomized multicenter clinical trials, patients with neck pain who meet the study standard are randomly divided into trial group and control group (subjects 1:1).

In the trial group, we used Shi’s cervical manipulation as the main intervention method. Shi’s manipulation intervention scheme was pre-tested in the experimental study of our research group. It was effective immediately after the shortest treatment time, and the longest treatment time was 12 weeks.

In the control group, we used oral administration of diclofenac sodium sustained-release capsules (Difene, manufacturer Temmler Ireland, Ltd.; 75 mg), the first-line non-steroidal anti-inflammatory drug to treat neck pain reported in the literature as the main intervention [11]. Clinical data collection will be completed in the Department of Orthopedics and Traumatology outpatient centers of Shuguang Hospital, Jing’an Center Hospital, and Xiangshan Hospital.

### Eligibility criteria {9}

The subjects of each research center participating in this study shall first meet the following diagnostic standards of acute and subacute neck pain [12, 13] and then determine eligibility according to the inclusion and exclusion criteria. The subjects included in this study shall carry out the follow-up study in strict accordance with the exclusion and removal criteria, and the specific operation route is shown in Fig. 1.

**Fig. 1 Fig1:**
[figure not shown]
Research flow chart

### Diagnostic criteria for acute and subacute neck pain [12, 13]

Primary symptom of mechanical, non-specific neck pain symptoms, with a duration of < 12 weeksPathologic criteria and degree criteria for neck pain: neck pain equivalent to grade I or II according to the Bone and Joint Decade 2000–2010 Task Force on Neck Pain and Its Associated Disorders classification (4 levels in total) [13];

Grade I neck pain: No signs or symptoms suggestive of major structural pathology, and no or minor interference with activities of daily living; will likely respond to minimal intervention such as reassurance and pain control; does not require intensive investigations or ongoing treatment.

Grade II neck pain: No signs or symptoms of major structural pathology, but major interference with activities of daily living; requires pain relief and early activation/intervention aimed at preventing long-term disability.

### Inclusion criteria

Age range from 18 to 65 years.The subjects meet the above diagnostic criteria for acute and subacute neck pain.NRS score of ≥ 3.It is an axial (non-root) neck pain caused by changes in the facet joints, discs, muscles, and ligaments [1].Those who are willing to participate in this experiment and sign the consent letter.

### Exclusion criteria

Cervical spine fracture and dislocationCervical vertebra, cervical soft tissue, cervical spinal cord tumor, and tuberculosis.Cervical spine fusion, paravertebral bridge, and severe osteoporosisA history of cervical spine surgeryA history of severe trauma to the cervical spine or neckNeck with skin inflammation, skin damage, etc.Patients with serious heart, liver, kidney, and hematopoietic system diseases; digestive system ulcer; bleeding; black stool; other diseases; and mental illnessPatients with extreme physical deficiency and pregnant womenParticipants who participated in clinical trials of other drugs and treatments within the previous 3 months that would interfere with this studyMeet grade III or IV according to the Bone and Joint Decade 2000–2010 Task Force on Neck Pain and Its Associated Disorders classification

Grade III neck pain: No signs or symptoms of major structural pathology, but the presence of neurologic signs such as decreased deep tendon reflexes, weakness, and/or sensory deficits might require investigation and occasionally more invasive treatments.

Grade IV neck pain: Signs or symptoms of major structural pathology, such as fracture myelopathy, neoplasm, or systemic disease; requires prompt investigation and treatment.

Those who meet 1 of the above conditions cannot be included in this study.

### Rejection criteria

Patients misdiagnosed as acute subacute neck painThe subjects mistakenly included (meeting the exclusion criteria)Those who did not receive treatment strictly and used drugs according to the regulations after being selectedNo detailed treatment recordThose who disobeyed the trial plan and combined with other drugsThose who still received other related treatment that affected the evaluation of this study at the time of selection and could not stop

Those who meet 1 of the above conditions should be rejected.

### Shedding criteria

Intolerable adverse reactions.Serious adverse reactions.The patients’ pain continued to increase, which proved that trial participation was not suitable.The patient’s health may be damaged (for example, serious complications).Those who voluntarily withdraw or miss visits in the middle.

Those who meet 1 of the above conditions should be shedding cases.

### Participants {26b}

Information and informed consent forms have been prepared in accordance with the guidelines of the China registered clinical trial ethics review committee. Potential participants receive both forms at least 1 day before their screening visit. During this visit, a study physician explains all study procedures, and written informed consent is only given after participants had adequate time to ask questions. We include male and female subjects with acute and subacute neck pain in this study. Each subject should voluntarily sign an informed consent form before testing begins in the study.

### Interventions

#### Intervention description {11a}

##### Trial group

The main intervention method in the trial group is Shi’s cervical manipulation therapy. The manipulation treatment team is composed of six clinicians (two in each of the three trial centers) with a minimum of 5 years’ experience in manual operation, who are good at manual spine diagnosis and treatment and have received standard operating procedures (SOP) training in this study. Each selected subject should have a 3-dimensional (3D) computed tomography (CT) reconstruction of the cervical vertebra, as well as a special physical examination of the cervical vertebra. Each subject will receive an initial diagnosis for 15–20 min after entering the group, including brief history collection, cervical static palpation (tenderness point and muscle spasm), cervical dynamic palpation (intervertebral looseness of the cervical spine), cervical sequence activity inspection, and cervical nerve reflex. Both history and examination results should be recorded in the case report form. According to the examination results, manipulation clinicians will give a comprehensive diagnostic analysis and manipulation therapy to each subject’s cervical spine. Key points of manipulation therapy operation are as follows: (1) acupoint pressing analgesia operation, according to the treatment principle of local acupoint selection and remote acupoint selection of cervical vertebra; point rubbing; and pressing operation are performed on the thumb pulp. The pressure can be light to heavy, then heavy to light, and the operation is repeated. The specific strength is to press until thumb nail color is white, while considering patient tolerance. Each acupoint is operated for 1 min. The specific acupoints are as follows: (a) local acupoints—Fengchi (International acupoint code GB20), Fengfu (International acupoint code DU16), Tianzhu (International acupoint code Bl10), Wangu (International acupoint code GB12), Dazhui (International acupoint code DU14), Jianjing (International acupoint code GB21), Jianzhongshu (International acupoint code SI15), Quepen (International acupoint code ST12), Tianzong (International acupoint code Si11), and Ashi; (b) remote acupoints—Lieque (International acupoint code LU7), Houxi (International acupoint code SI3), and Hegu (International acupoint code LI4). (2) Bone-setting manipulation operation, according to the results of palpation and 3D CT reconstruction of the patient’s cervical spine, the clinicians will give directional and fixed-point bone-setting manipulation to treat the cervical vertebrae semidislocation. The specific operation is as follows: the patient sits on the treatment chair, with the head slightly bent forward, and the manual operation physician stands at the patient’s side, with the right side as the patient’s side, for example, the manual operation physician locks his left thumb against vertebral plate between the transverse process and the spinous process of the cervical vertebra with semidislocation, and the other four fingers stick to the patient’s left head and neck, and the middle and upper part of the elbow of the right arm slightly bent on the patient’s lower jaw, according to the vertebrae semidislocation direction, the left thumb with pushing force to the vertebral plate in the opposite direction of semidislocation, while the right forearm rotates rapidly to lift and rotate the head with a direction- and size-controlled flashing force. There is a sliding motion and snapping sound from the vertebra under the left thumb. The whole manual operation treatment lasts for 20 min each time, and is done twice a week, with the longest course of treatment lasting for 12 weeks.

##### Control group

The main intervention method in the trial group is oral NSAIDs. Each selected subject should have a 3D CT reconstruction of the cervical vertebra, as well as a special physical examination of the cervical vertebra. The treatment team is composed of three clinicians (one in each of the three trial centers) with the qualification of clinical medical registered doctors and senior professional titles, who have received SOP training in this study. After exclusion of the contraindications of diclofenac sodium (known to be allergic to other components of diclofenac sodium, acetylsalicylic acid, ibuprofen, and Daphne, gastric and duodenal ulcer, gastrointestinal inflammatory disease, black stool, or unknown blood history), the NSAID diclofenac sodium double-release enteric-coated capsules (Difene, manufacturer Temmler Ireland. Ltd.; 75 mg, once a day, once a time, oral) is the main intervention. Each subject will receive an initial diagnosis for 15–20 min after entering the group, including brief history collection, cervical static palpation (tenderness point and muscle spasm), cervical dynamic palpation (intervertebral looseness of the cervical spine), cervical sequence activity inspection, and cervical nerve reflex. Both history and examination results should be recorded in case report form. Each subject will obtain a patient log card, which shall be kept by the patients themselves (handed over to the physician in charge of the group at the end of the test), and will be used to record name, dose, time, discomfort, combined medication, and other information about the drug taken truthfully every day. The specific drug dosage shall be specified by the physician in charge of the group according to the drug use instructions, and the maximum duration of the medication shall be 12 weeks.

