#### Subject recruitment {15}

According to the sample size requirements of 120 cases in the trial group and the control group, this project uses written and online media promotion, broadcast, and other ways to recruit subjects with neck pain to visit Orthopedic Department Outpatients of Shuguang Hospital, Jingzhong Hospital, and Xiangshan Hospital according to the principles of convenient transportation and proximity. The subjects need to go through two baseline diagnostic screenings by clinicians in each research center. The clinicians in charge of diagnosis and screening are not aware of the random grouping. During the scheduled clinical visit, the study clinicians will provide a brief overview of the study. If the participant is interested, the clinicians will determine patient eligibility according to the above eligibility criteria. If the patient is eligible and agrees to participate, the clinicians will conduct the informed consent and enrollment. Participants will be able to discuss study details with the clinicians and ask questions before signing the informed consent. Following enrollment, participants will be randomized by the assistants, who are full-time research assistant in charge of patient grouping, accept their cervical spine examination and imaging examination, and receive the assigned treatment.

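### Some diclofenac contraindications stand only in the control-group text, and imaging that several exclusions depend on is placed after randomisation

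*Protocol article*

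**What the plan says.** **Common exclusions.** The Exclusion criteria apply to every candidate. Their gastrointestinal items are "digestive system ulcer; bleeding; black stool". They also list conditions usually recognised on imaging: fracture and dislocation, tumour, fusion, paravertebral bridge and severe osteoporosis.

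**Control-arm check.** Intervention description {11a}, Control group, gives diclofenac "After exclusion of the contraindications of diclofenac sodium (known to be allergic to other components of diclofenac sodium, acetylsalicylic acid, ibuprofen" and so on; the list continues with "gastric and duodenal ulcer, gastrointestinal inflammatory disease, black stool, or unknown blood history". The Trial group section has no such step.

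**Order of events.** In Subject recruitment {15}, "the clinicians will determine patient eligibility according to the above eligibility criteria", and consent and enrolment follow. Participants are then randomised by the assistants, and after that "accept their cervical spine examination and imaging examination, and receive the assigned treatment".

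**Imaging by arm.** The requirement is the same in both. Trial group: "Each selected subject should have a 3-dimensional (3D) computed tomography (CT) reconstruction of the cervical vertebra". Control group: "Each selected subject should have a 3D CT reconstruction of the cervical vertebra". The note to Fig. 2 accepts an imaging report from the previous 3 months.

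**Later removal.** The Rejection criteria remove anyone included by mistake who meets an exclusion criterion. Under Statistical methods {20a}, the full analysis set is mainly all randomised subjects after an elimination that is not defined. The safety set requires at least one use of the drug or receipt of manual treatment, and at least one follow-up record.

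**The concern.** Whether a person may enter the trial should be settled before the arm is known, and by the same test in both arms. Two parts of the protocol depart from this.

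First, part of the contraindication list is tied to the diclofenac arm. If controls who fail that check drop out of treatment or analysis, people of the same kind in the manipulation arm do not, and the arms are no longer fully comparable. A patient may also be allocated to a drug that the protocol itself lists as contraindicated for them.

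Second, if imaging is read after randomisation, an exclusion found on it becomes a loss after allocation that earlier review would have avoided.

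Both bear on the trial's efficacy hypothesis and on its hypothesis that manipulation is safer than NSAIDs.

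**Working it through.** The point rests on no figure in the plan, so the check is mainly a comparison of sections.

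**Step 1. Which contraindications are common to both arms?**

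| Condition | Exclusion criteria (all) | Control group text |
|---|---|---|
| Digestive ulcer | named | named |
| Black stool | named | named |
| Bleeding | named | not named as such |
| Hypersensitivity to diclofenac components, acetylsalicylic acid or ibuprofen | not named | named |
| Gastrointestinal inflammatory disease | not named | named |
| Unknown blood history | not named | named |

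Three entries are therefore confined to the control-group text.

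**Step 2. When is that check made?** The protocol does not time it against randomisation. It stands among the arm's treatment steps, and the same section places brief history-taking after the subject has entered the group. Someone with one of the three conditions can satisfy the inclusion and exclusion criteria and be randomised.

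**Step 3. What follows for a control who fails?** Nothing is stated. The Rejection criterion for mistaken inclusion refers to the exclusion criteria, and these three entries are not among them, so that rule does not settle the case. A control stopped before any diclofenac is taken has had no study treatment and falls outside the safety set; a similar patient who receives manipulation and has a follow-up record stays in it. The undefined elimination leaves the full analysis set open.

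**Step 4. Imaging.** The stated order is eligibility, consent, enrolment, randomisation, examination and imaging, treatment. Several exclusions depend on the fifth step, and the Rejection criteria then remove those found to meet them. The CT requirement and the removal rule are the same in both arms.

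**Step 5. Size, for illustration.** The documents give no prevalence. Assume that a fraction f of 2% to 5% of controls have one of the three conditions and are lost.

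- Controls lost: 120 × 0.02 = 2.4; 120 × 0.05 = 6.
- Power: Φ(0.58 / √(1.70²/120 + 1.65²/n₂) − 1.96), with the SDs and the difference 2.08 − 1.50 = 0.58 from Sample size {14}, before any other loss. With n₂ = 120 this is 76.5%; with 117.6, 76.1%; with 114, 75.4%. (The starting value is a plain superiority reading of the stated inputs. Its distance from the planned 90% is a separate matter.)
- Shift in the control mean if those lost differ from those kept by D points: f × D. For D = 1 this is 0.02 to 0.05, or 3% to 9% of 0.58. For D from 0.5 to 2 it runs from 0.01 to 0.10. The values of D are assumptions too.

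**The case against.** The case against is substantial, and much of it limits the point.

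- A reader might infer that diclofenac contraindications in general are screened in the control arm only. The documents do not support that: ulcer, bleeding and black stool, and serious heart, liver, kidney and haematopoietic disease, exclude everyone. The common list also has an unspecified entry for other diseases, which might be stretched to gastrointestinal inflammatory disease, though hardly to drug allergy.
- A reader might infer that imaging exclusions differ by arm. CT, examination and removal rule are the same in both. Different clinicians treat each arm and the treating physician learns the allocation, so unequal application is possible, but nothing shows that it occurs.
- A reader might infer that the control arm loses its NSAID-intolerant patients, so that the arms come from different populations. Removal of controls who fail the check is not stated, and the full analysis set is described as close to all randomised subjects.
- Figs 1 and 2 are not shown. Two baseline screenings and the 3-month allowance mean that some imaging may exist before randomisation. The evidence for the late timing is the order of one sentence in Subject recruitment {15}.
- The check does precede the drug, so the text does not have contraindicated patients taking it.
- The effect on power is slight. If NSAID-intolerant controls were lost, recorded diclofenac harms would tend to fall, which works against the trial's own safety hypothesis.

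All of this stands, yet the core remains. Three listed contraindications are absent from the common criteria, the fate of a control who fails is undefined, and the stated sequence conflicts with settling eligibility before enrolment.

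**Conclusion.** The concern holds in two limited parts. Hypersensitivity to diclofenac components, acetylsalicylic acid or ibuprofen, gastrointestinal inflammatory disease and unknown blood history are checked in the control-group text only, with no stated consequence for a control who fails. Separately, imaging on which common exclusions rest is placed after randomisation, which risks avoidable removals in both arms under a common rule.

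The number affected cannot be derived from the documents, and the 2 to 6 controls above rest wholly on the assumed 2–5%. The loss of power would be about one percentage point at most on that assumption. The reasons to act are comparability of the arms, above all for safety, and the avoidable allocation of patients to a drug listed as contraindicated for them. The reading of the imaging sequence is subject to the figures that are not shown.

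**What to change.** Reconcile the Exclusion criteria, the Rejection criteria, the Control group text, Subject recruitment {15} and Statistical methods {20a} as follows.

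1. Apply the protocol's own contraindication list to all candidates as part of the common exclusion criteria. Its content remains for the clinicians.
2. Require that the list, the cervical examination and the imaging report (new, or from within 3 months as the Fig. 2 note allows) are reviewed before the random number is requested.
3. State that anyone found ineligible on these grounds after randomisation stays in the full analysis set, and word the Rejection criteria and the elimination clause so that they do not override this.

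The cost is a re-ordered screening visit, revised eligibility wording and slightly more screen failures. The examinations are those already required, done earlier.
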